**Enrolment**				
Eligibility screen	X			
Information to patients/careviger	X			
Collection of consent	X			
Date of the visits	X	X	X	X
**Assessments**				
*Primary outcome:*				
Unplanned Hospitalizations			X	
*Secondary outcomes:*				
Unplanned Hospitalizations				X
Behavioral disorders (NPI)		X	X	X
Quality of life (EQ-5D-3 L)		X	X	X
Number of falls		X	X	X
Number of patients with at least 1 potentially inappropriate prescription		X	X	X
Nursing staff satisfaction		X	X	
Characteristics of patients whose GP have taken account of TMR recommendations			X	X
GP’ adherence rate to therapeutic recommendations			X	X
Cost-effectiveness ratio of TMR				X
Factors facilitating or hampering GPs’ adherence rate		X	X	X
**Characteristics**				
Sociodemographic data (age, gender)	X	X		
MMSE	X			
Comorbidities		X	X	X
Pharmaceutical therapeutics		X	X	X
Blood test		X	X	X
Trivalle’s score	X			

### Inclusion criteria

Predefined inclusion criteria are that participants must: be at least 65 years old; live in a nursing home; have a Trivalle’s score of between 2 and 10; and be affiliated to the French public welfare system.

The patient or informal caregiver or legal representative will sign the informed consent form prior to randomization.

### Exclusion criteria

Patients who exhibit any of the following criteria will be excluded: life expectancy < 3 months; involvement in another research project; medication review conducted by a pharmacist in the last 6 months; mini mental state examination (MMSE) score < 18 [22].

Refusal to participate on the part of general practitioner (GP) constitutes a secondary exclusion criterion in this study.

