### Recruitment and randomization

Recruitment will take place within consenting nursing homes contacted by the gerontology coordination groups of Marseille. Nursing home coordinating physicians will act as study investigators in charge of patient inclusion. Written consent to participate will be obtained at the Nursing home after the investigator has provided all necessary information about the study. Randomization will be performed at patient level, with eligible patients randomly assigned in a 1:1 ratio to the control group (non-intervention) or the experimental group (TMR) based on a computer-generated permuted-block randomization schedule with blocks of four. Randomization is to be stratified by an adverse drug event risk detection score in elderly patients, the Trivalle’s risk score (≤ 5 or > 5). Based on the IMEPAG study [21], this score is both easy and practical to use for detecting the risk of adverse drug events in elderly patients. Risk factors included in the score are: number of medications (if greater than or equal to 7), antipsychotic treatment and recent anticoagulant treatment (dating back less than 3 months). Each parameter is scored on a scale from 0 to 10, with 0–1 corresponding to an adverse drug event risk of 12%, 2–5 corresponding to a 32% risk and 6–10 to a 53% risk.

Computer-generated randomized lists will be drawn up before the beginning of the study under the responsibility of the local Clinical Research Unit. Methodological support will be provided by the Clinical Research Unit. Study investigators will not be blinded to group allocation. The recruitment period will span 20 months, and patient follow-up will last 6 months (Table 1).

**Table 1 Tab1:** Timeline of the study

Timepoint	Study Period			
	Enrolment	Inital assessment	Follow-up at 3 months	Follow-up at 6 months

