### Groups

#### Experimental group

Patients randomized into experimental group will benefit from TMR undertaken by a hospital-based team composed of a clinical pharmacist and a geriatrically-trained internal medicine specialist. For the purposes of issuing quality validation and relevant guidelines, TMR requires:
medication reconciliation to have an exhaustive list of all medications taken by the patient (including prescription and non-prescription medication);inclusion of the most recent results from laboratory tests (blood sodium, potassium and creatinine levels) and clinical data (blood pressure, weight);knowledge of patient history, active comorbidity and geriatric syndromes.

TMR means undertaking multidisciplinary medication reviews and taking into consideration all available sociodemographic, clinical, biological and pharmaceutical data pertaining to patients to optimize their therapeutic management.

It should be noted that an exhaustive list of patient medications will be acquired through medication reconciliation in accordance with the guidelines of French National Authority for Health [25].

Each drug prescription will be assessed in light of patient medical conditions, level of dependence and quality of life (amount, dosage, route of administration, contra-indications, drug interaction, and precautions for use). Medication databases will be consulted, following which adjustments to prescriptions can be made using the explicit criteria from STOPP/START.v2 criteria coupled with an implicit approach (the Medication Appropriateness Index) and taking into consideration existing therapeutic guidelines. A written report summarizing any proposed therapeutic adjustments will be produced and officialized as a personalized pharmaceutical plan (PPP) signed by both physician and pharmacist. The conclusions resulting from TMR will be transmitted to healthcare professionals within a maximum of 5 days after patients have been randomized to the experimental group. Should a therapeutic error with repercussions for patient prognosis be detected, the coordinating physician and patient’s GP will be informed immediately by phone. The GP can accept or reject the medication adjustments proposed by TMR. Data relevant to the study will be collected at the inclusion, 3 and 6 months.

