### Data management and analysis

Data will be monitored by a clinical research monitor. Inconsistencies will be reported to the study investigators in order to decide whether the data should be corrected or considered as missing data. Statistical analysis will be performed after checking the database. After freezing, the consolidated data will be processed by statistician. The modified intention-to-treat population (including all randomized subjects evaluated at least at baseline; patients having withdrawn consent will be excluded from the final analysis) will be used in the primary analysis. No interim analysis is planned. Baseline parameters will be presented by group (control and experimental). No comparisons will be made in accordance with CONSORT guidelines.

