The cost perspective taken in our economic analysis is that of the healthcare payer. The time horizon starts at the first baseline evaluation and ends at 6-month follow-up. This horizon is pertinent for recording immediate and relevant healthcare utilization and costs associated with the innovative strategy and represents a period during which all effectiveness and cost data will be accurately collected. The healthcare resources included will be those that are likely to differ between the experimental and control groups and will consist of: the TE intervention (including all categories of staff involved in data analysis and PPP writing, equipment required, time taken by coordinator/physician to collect and transfer data) and the healthcare costs generated by follow-up (including pharmaceutical medications and associated treatments, unplanned consultations and examinations, emergency department visits, inpatient stays differentiating between planned and unplanned hospital admissions, and transport costs). All resources will be collected from patient medical records and where necessary from referred hospital Departments of Medical Information (DIM) to identify exhaustive use of inpatient resources. Unit costs will be estimated using data from the French National Hospital Database and the national tariff. Medication costs will be obtained from the French Register of Pharmaceutical Specialties, an online database providing information on healthcare products. All resources will be valued in 2020/2021 euros, and the 6-month trial period means that no application of discount is required.

Descriptive statistics will be used to analyze effectiveness and cost variables, being both univariate and multivariate analysis (using non-parametric tests and bootstrap procedures respectively). Reweighted survival estimators and repeated measures of health-related QoL will be used in case of censored data. Probabilistic sensitivity analyses, using the non-parametric bootstrap method, will be carried out to generate mean expected ICERs and to determine whether uncertainty or variation in the data used affect the ICERs [31]. In addition, cost-effectiveness acceptability curves will be constructed to represent decision uncertainty surrounding cost-effectiveness estimates [32].

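### Withdrawn patients are dropped from the primary analysis set, and exclusion for GP refusal is not timed against randomization or reconciled with that set

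*Protocol article*

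**What the plan says.** **Analysis set.** Data management and analysis defines the modified intention-to-treat population as "including all randomized subjects evaluated at least at baseline; patients having withdrawn consent will be excluded from the final analysis", and states that this population "will be used in the primary analysis". Withdrawal of consent is the only removal it names; GP refusal is not mentioned.

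**GP refusal.** Exclusion criteria lists the patient-level exclusions and then adds, as a separate sentence, "Refusal to participate on the part of general practitioner (GP) constitutes a secondary exclusion criterion in this study". It does not say whether refusal is established before or after allocation.

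**What is tied to the time before randomization.** Inclusion criteria says "The patient or informal caregiver or legal representative will sign the informed consent form prior to randomization". No corresponding statement is made for the GP.

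**Knowledge of allocation and arm-specific contact.** Study design calls the trial single-blind, while Recruitment and randomization says "Study investigators will not be blinded to group allocation". The review's conclusions go out within 5 days of allocation, in the experimental arm only (Experimental group). Control patients have no medication review (Control group). GPs are paid only for experimental-arm patients (Discussion).

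**Rejecting advice is a different matter.** Within the experimental arm, "The GP can accept or reject the medication adjustments proposed by TMR". Adherence to the recommendations is a secondary endpoint.

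**The concern.** Randomization protects the comparison only while patients stay in the analysis regardless of what happens after allocation. Two rules in this plan may break that.

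The withdrawal rule is explicit. It removes a patient because of an event after randomization and makes no provision for keeping what was recorded beforehand. A resident admitted in week 3 who withdraws in week 6 has had the primary event, yet disappears from both numerator and denominator. Because only one arm is asked to consider changes in medication and investigators know the arm, the reasons for withdrawing, and hence the risk of those who withdraw, may differ between arms.

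The GP rule is ambiguous. If refusal is settled before randomization, it is an ordinary eligibility condition and harmless to the comparison. If it can be invoked afterwards, it is an exclusion after allocation at a point where the GP's involvement differs by arm. Two statisticians working from this text could build different primary sets.

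At stake is whether the primary relative risk is a comparison of the groups as randomized.

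**Working it through.** **1. The plan's own figure.** Inputs from Sample size: 25% versus 10%, two-sided 0.05, 90% power. With a pooled rate of 0.175:

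n = [1.960·√(2·0.175·0.825) + 1.282·√(0.25·0.75 + 0.10·0.90)]² / 0.15² = 132.8, or 133 per arm.

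The continuity correction, (n/4)·[1 + √(1 + 4/(n·0.15))]², gives 145.8, or 146 per arm. The total is 292, as stated. The 25% control rate and 182 per arm are used below.

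**2. The two sections side by side**, for a randomized, baseline-evaluated patient:

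| Event after randomization | Exclusion criteria | Analysis-set definition |
|---|---|---|
| Consent withdrawn | not addressed | removed |
| GP refuses to participate | excluded, timing unstated | kept (not a named removal) |
| GP rejects recommendations | not an exclusion | kept; adherence measured |

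The first row is a stated rule. The second is a conflict if refusal can occur after allocation. The third is in order.

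**3. How much bias could removal cause?** The documents give no withdrawal or refusal rate, so everything here is assumed: no true effect, 25% risk in both arms, and a fraction f removed from the experimental arm only, with risk r among those removed.

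Retained experimental risk = (0.25 − f·r)/(1 − f); apparent RR = that risk / 0.25.

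| f | r | Retained risk | Apparent RR | Two-sided rejection |
|---|---|---|---|---|
| 10% | 15% | 0.235/0.90 = 26.1% | 1.04 | 5.7% |
| 10% | 25% | 0.225/0.90 = 25.0% | 1.00 | 5.0% |
| 10% | 35% | 0.215/0.90 = 23.9% | 0.96 | 5.6% |
| 10% | 40% | 0.210/0.90 = 23.3% | 0.93 | 6.5% |
| 20% | 15% | 0.220/0.80 = 27.5% | 1.10 | 8.1% |
| 20% | 25% | 0.200/0.80 = 25.0% | 1.00 | 5.0% |
| 20% | 35% | 0.180/0.80 = 22.5% | 0.90 | 8.1% |
| 20% | 40% | 0.170/0.80 = 21.3% | 0.85 | 12.4% |

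Rejection is for the uncorrected two-proportion z-test with 182 controls and 182·(1 − f) experimental patients. A more extreme assumption, 20% removed at 50% risk, gives RR 0.75 and 26.9% rejection. Under the same null, removal of the same fraction at the same risk from both arms leaves RR at 1.

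**4. What keeping everyone would cost.** Assume a fraction f of the experimental arm has a non-cooperating GP and gets no benefit. The expected experimental rate is 0.10·(1 − f) + 0.25·f, that is 11.5% at f = 10% and 13.0% at f = 20%. Power by the uncorrected test:

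| Per arm analysed | f = 0 | f = 10% | f = 20% |
|---|---|---|---|
| 182 (complete follow-up) | 97% | 92% | 83% |
| 146 | 93% | 85% | 75% |

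**The case against.** The strongest reply is that the GP half is not established. The sentence sits under Exclusion criteria, and randomization is of eligible patients, so a reading before randomization is at least as natural. Exclusion after inclusion need not mean exclusion after allocation, and the timing of GP contact is a detail a condensed article may leave to the full protocol. The analysis-set definition does not remove patients for GP refusal. All this stands: post-allocation exclusion for GP refusal is possible on the text, not stated. What remains is that the wording does not settle the matter and the two sections do not fit together if it occurs late.

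A reader might go further in three ways that the documents do not support:

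- **That the plan excludes the very event it sets out to measure.** Refusing to take part is not the same as rejecting advice. Patients whose GP rejects recommendations stay in, and adherence is an endpoint.
- **That refusal will arise mainly in the experimental arm.** No pattern of refusal is documented, and paying GPs for those patients could equally reduce refusal there.
- **That removal makes the intervention look better.** Bias is nil if those removed have average risk and reverses if their risk is low.

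It is also fair to say that at 10% removal and 15–40% risk the spurious RR lies between 0.93 and 1.04, small beside the design RR of 0.10/0.25 = 0.40. That limits the size of the problem. It does not justify the withdrawal rule, which is explicit and needs no inference about timing.

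**Conclusion.** The concern holds in two parts of unequal strength. The exclusion of withdrawn patients from the primary analysis is a stated rule that conditions on a post-randomization event, with investigators unblinded and proposed medication changes in one arm only; it should be changed. The GP-refusal sentence and the analysis-set definition need reconciling, because the text allows, but does not state, exclusion after allocation.

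Neither the size nor the direction of bias can be derived from the documents. Under one-sided removal of 10–20% and a true null at 25%, the apparent RR is about 0.85–0.96 if those removed have 35–40% risk, 1.0 at average risk, and 1.04–1.10 at 15% risk. These figures rest wholly on assumed fractions and risks and show a range, not an estimate.

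**What to change.** 1. **GP refusal.** State that GP agreement is established before randomization, and that no randomized patient is removed from the analysis for later GP refusal. The article reports enrolment since April 2019, so for patients already randomized only the second half can apply.
2. **Primary set.** Define it as all randomized patients in their allocated arm, and state that the baseline assessment is completed before allocation, so that requiring it cannot act as a post-randomization filter.
3. **Withdrawal.** Use data collected up to withdrawal unless the patient objects. An admission already recorded then counts. The planned Kaplan–Meier analysis can take the remaining patients as censored; the analysis plan should say how they enter the binary comparison.
4. **Reporting.** Give all post-randomization exclusions by arm and reason.

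The cost is wording in the protocol and analysis plan, and GP contact moved ahead of randomization where it now comes later. No new data source is needed for events before withdrawal, since Study procedures already names resident medical records. The downside is some dilution by non-cooperating GPs, at the power shown in step 4 of the working. Obtaining agreement before randomization should keep that fraction small.

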### Ethical and legal considerations

The protocol has been approved by the regional ethics committee (*Comité de protection des personnes Sud Est II*) on 21 November 2018. Data processing has been approved by the national data protection commission.

### Sample size

On the basis of a unplanned hospital admission rate of 25% over a 3-month period [23] and taking into consideration the results of a study evaluating the impact at 8 weeks of medication review on admission to nursing home [24], we estimate a unplanned hospital admission rate of 10% in the experimental group. The initial sample size of 292 patients provided 90% power to detect this difference at a two tailed significance level of 0.05. Assuming possibly 25% of patients lost to follow-up, a total of 364 patients is required (182 per group) (Fig. 1).

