**Methods:**

The present study is a randomized controlled clinical trial. A total of 364 patients will be randomized into two groups: (1) an experimental group (182 patients) benefiting from a telemedication review using tele-expertise and (2) a control group (182 patients) receiving standard care. The primary endpoint will be rate of all-cause unplanned hospital admissions occurring within 3 months of randomization. The secondary endpoints will be rate of unplanned admissions at 6 months, patient quality of life, incidence of behavioral disturbances, number of falls, number of residents prescribed at least one inappropriate medication, nursing staff satisfaction, proposed medication reviews and their acceptability rate, characteristics of patients whose general practitioners have taken account of tele-expertise, efficacy of tele-expertise as compared to standard prescription and acceptability and satisfaction surveys of participating caregivers.

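### The 25% loss allowance is added to 292 instead of being divided out, so 364 randomised patients do not leave the 292 that the stated 90% power needs

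*Protocol article*

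**What the plan says.** The Sample size section assumes an "unplanned hospital admission rate of 25% over a 3-month period" under standard care and, for the intervention, "we estimate a unplanned hospital admission rate of 10% in the experimental group". It continues: "The initial sample size of 292 patients provided 90% power to detect this difference", "at a two tailed significance level of 0.05". The allowance for attrition follows: "Assuming possibly 25% of patients lost to follow-up, a total of 364 patients is required (182 per group").

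The Methods part of the Abstract repeats the total: "A total of 364 patients will be randomized into two groups", with 182 in each. The article does not give the formula behind 292 or the one used to inflate it, and states no other loss rate.

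**The concern.** A loss rate expressed as a share of the patients is a share of those randomised. The number to randomise is therefore the evaluable number divided by one minus the loss rate. Multiplying the evaluable number by one plus the loss rate gives too small a total, and the gap widens as the rate rises. At 25% the two routes differ by about 25 patients here, and 364 lies next to the wrong one.

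What is at stake is the main justification of the trial's size. A reader who sees 25% loss, 90% power and 364 randomised will take it that the trial keeps 90% power if attrition reaches the planned level. Under the calculation that gives 292, it does not. This matters most if the result is null or if attrition comes close to 25%.

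**Working it through.** **Inputs.** All come from the Sample size section unless noted: p₁ = 0.25 (control), p₂ = 0.10 (experimental), two-sided α = 0.05, power 0.90, 292 evaluable, 25% loss, 364 randomised. Allocation is 1:1 (Recruitment and randomization). The primary test is chi-square or Fisher's exact (Data management and analysis, Primary endpoint).

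**Step 1: reproduce 292.** With p̄ = 0.175 and d = 0.15, the pooled-variance formula is

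n = [1.960 × √(2 × 0.175 × 0.825) + 1.2816 × √(0.25 × 0.75 + 0.10 × 0.90)]² / 0.15²
= (1.0532 + 0.6751)² / 0.0225 = 132.8 per group.

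Rounded up this is 133 per group, or 266 in total, which does not match. With the continuity correction,

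n_cc = (n/4) × [1 + √(1 + 4/(n × d))]² = (132.76/4) × (1 + 1.0958)² = 145.8, so 146 per group, or **292** in total.

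That is an exact match. The unpooled (260) and arcsine (258) versions do not match, nor do the one-sided or 80%-power versions. The continuity-corrected formula is therefore very probably the one used.

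**Step 2: the inflation.**

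| Calculation | Result |
|---|---|
| 292 × 1.25 | 365 (182.5 per group; 182 per group gives 364) |
| 292 / (1 − 0.25) | 389.3, so 390 (195 per group) |
| 364 × (1 − 0.25) | 273 evaluable |
| 292 − 273 | 19 short |
| 1 − 292/364 = 72/364 | 19.8%, the largest loss that still leaves 292 |

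Rounding accounts for 365 becoming 364. It does not account for the 26 patients between 364 and 390.

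**Step 3: power at 273 evaluable (136.5 per group).**

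- By the continuity-corrected formula, 136.5 per group corresponds to an uncorrected n of 123.5. Then z = (0.15 × √123.5 − 1.0532) / 0.5268 = 1.165, and power is **87.8%**. The same inversion at 146 per group gives 90.0%.
- By the uncorrected pooled formula, power at 136.5 per group is 90.8%.
- Exact enumeration over the two binomial distributions gives:

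| Evaluable (control / experimental) | Uncorrected chi-square | Fisher's exact | Continuity-corrected chi-square |
|---|---|---|---|
| 137 / 136 | 91.4% | 89.4% | 88.7% |
| 136 / 137 | 91.7% | 91.0% | 88.5% |
| 146 / 146 (as intended) | 93.3% | 90.9% | 90.6% |

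The Fisher figure moves by 1.6 points with the placement of the odd patient because the test is discrete.

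**The case against.** The strongest reply is that little is lost. The analysis section names a chi-square or Fisher's exact test and mentions no continuity correction. An uncorrected chi-square needs only 266 patients, so 273 would still give more than 90% power. The drop to 87.8% rests on a formula that is inferred and not stated. This is right about the size of the effect. It does not reconcile the figures: the plan itself attaches 90% power to 292, and 273 is not 292 under any test.

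A second reply is that 273 assumes every lost patient has no primary outcome. The modified intention-to-treat population keeps all randomised patients evaluated at least at baseline, apart from those who withdraw consent. Admissions are read from residents' medical records, so the 3-month status of some patients who leave follow-up may still be known. That could make the real shortfall smaller. However, the sample-size sentence treats the 25% as patients who must be made up for. If most of their outcomes can be recovered, 25% is the wrong allowance and the sentence still needs changing.

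It cannot be put down to a condensed article, since the point concerns a printed figure and not an omitted detail.

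**Conclusion.** The statement is wrong as written. 292 evaluable, 25% loss and 364 randomised cannot all hold. With 364 randomised and 25% lost, 273 remain, 19 short; 364 protects 292 only up to a loss of 19.8%.

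The practical effect is small. Power falls by about 2 points (87.8% against 90%) by the formula that reproduces 292. Exact power at 273 ranges from 88.5% to 91.7% according to the test and the split between arms, and it stays above 90% with an uncorrected chi-square. These figures take the planned rates of 25% and 10% as given, assume equal loss in both arms, and assume that lost patients have no primary outcome. The design is not seriously underpowered; the error lies in the stated justification.

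**What to change.** Keep 364 and correct the sentence in one of two ways:

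- state that 364 allows for about 20% loss (19.8% leaves 292; 20% leaves 291), with 90% power; or
- keep the 25% allowance and state that it leaves 273 evaluable patients, with about 88% power by the continuity-corrected calculation.

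In either case, name the continuity-corrected formula behind 292, so that the figure can be checked. Holding both 25% loss and 292 evaluable would take 390 randomised (195 per group), but a gap of about 2 points does not call for that.

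The cost is one sentence in the protocol, carried into the SAP if it repeats the calculation. The Abstract total of 364 stays as it is. The stated loss allowance or power becomes slightly less favourable, and enrolment and analysis do not change.
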